**SUMMARY**

According to the Framework for Clinical Evaluation of Devices for Adult Male Circumcision (WHO, 2011): *“WHO and other health authorities wish to identify one or more devices that (a) would make the VMMC safer, easier, and quicker; (b) would have more rapid healing than current methods and/or might entail less risk of HIV transmission in the post-operative period; (c) could be performed safely by health-care providers with a minimal level of training; and (d) would be cost-effective compared to standard surgical methods for male circumcision scale up.”*

Because of difficulties and small risks entailed in using sterilizable instruments, WHO prefers disposable, single-use-only instruments be used for circumcision. This proposed randomized controlled trial will provide important data which will inform and enable the South African health system to more effectively scale-up circumcision services. This study will prove that VMMC using the Unicirc disposable single-use-only instrument coupled with tissue adhesive meets WHO criteria for the ideal method: it is faster, easier to learn, safer for both surgeons and patients, heals sooner, has excellent cosmetic results, and is more cost effective than any other currently available technique.

We propose a randomized controlled trial (RCT) comparing this minimally-invasive circumcision technique to the open surgical technique. In accordance with WHO recommendations concerning sample size found in the Framework for Clinical Evaluation of Devices for Adult Male Circumcision, we propose to study:

- Unicirc disposable instrument with topical anaesthetic and tissue adhesive wound sealing: 50 men
- Open surgical circumcision: 25 men

This is the fourth study of Unicirc circumcision, and the second study that uses topical anaesthetic instead of injectable local anaesthetic. Tissue adhesive is widely used in multiple areas of medicine; specifically, multiple observational studies and RCTs have shown cyanoacrylate tissue adhesives to be superior to suture closure in VMMC. The open surgical method will serve as the control intervention.

*Population:* Men at least 18 years of age who desire male circumcision

*Study design:* Randomized controlled trial

*Intervention:* Unicirc instrument circumcision plus tissue adhesive vs. open surgical circumcision

*Follow-up visits:* 7 days and 28 days. Optional 42 day follow-up if not completely healed by 4 weeks.

*Primary outcome:* Intraoperative time

*Secondary outcomes:* Complications (operative and post-operative); time to healing; direct costs; post-operative pain; patient satisfaction; cosmetic result.

Protocol, UNICIRC clinical trial 004

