**Must all be YES to participate?**

- Requests circumcision and would potentially like to be part of a study? Yes ☐ No ☐
- At least 18 years of age? Yes ☐ No ☐
- Able to provide informed consent to participate? Yes ☐ No ☐
- Willing to participate in 2 follow-up visits? Yes ☐ No ☐
- Generally healthy? Yes ☐ No ☐

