### Post-Operative Instructions Unicirc

Participant ID \_\_\_\_\_

If you have complications or questions, call the Doctor.

Doctor's name and phone contact \_\_\_\_\_

Phone number of Medical Centre \_\_\_\_\_

- Swelling is normal in the first week, but if the wound hurts or swells more or gets redder, call the doctor.

- Take paracetamol, two tablets every 4-6 hours when needed for pain (up to 8 tablets per 24 hours)

The adhesive tape (Hypafix) should remain in place for 7 to 10 days, until it falls off. If it has not fallen off by 2 weeks, wet the area and remove it gently.

How to care for your wound:

- Leave only the tape as a dressing. The tape should stay dry.

- You may wash briefly but do not soak or scrub the area. To dry, rub gently with a soft towel.

- Avoid ointments. Do not apply creams or lotions, creams, Vaseline or any other product to the wound.

- Do not rub, scratch or pick at the wound.

- Redness, swelling and pain are common at first, and should be less every day. Contact us if there is increased redness, swelling or pain, if the wound is hot to the touch, or if the wound edges reopen or separate.

| Follow-up visits   | Date |
|--------------------|------|
| 7 days             |      |
| 4 weeks            |      |
| 6 weeks (optional) |      |

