**WOUND HEALING**

5. Did the participant have any difficulty keeping the wound clean and dry? .....   
0 = No  
1 = Yes  
**5a. If YES, describe:** \_\_\_\_\_  
\_\_\_\_\_

6. Has the wound completely healed (no wound, completely epithelialized)? .....   
0 = No  
1 = Yes → **SKIP REST OF QUESTIONS**

7. Is there wound disruption or dehiscence?.....   
0 = None    1 = < 2cm  
2 = More than 2 cm

8. Is there any swelling?.....   
0 = None    2 = Moderate  
1 = Mild    3 = Severe (if severe, complete AE form)

For Questions 9-13, if response is "moderate" or "severe," complete AE form and take a photo with participant's permission.

9. Is there any evidence of infection?.....   
0 = None    2 = Moderate  
1 = Mild    3 = Severe

10. Is there any bleeding?.....   
0 = None    2 = Moderate  
1 = Mild    3 = Severe

11. Is there a hematoma?.....   
0 = None    2 = Moderate  
1 = Mild    3 = Severe

12. Does the participant report difficulty or pain with urination? .....   
0 = None    2 = Moderate  
1 = Mild    3 = Severe

13. Are there any other complications?.....   
0 = None    2 = Moderate  
1 = Mild    3 = Severe

**13a. If response is 1, 2, or 3, describe complication:** \_\_\_\_\_  
\_\_\_\_\_

14. Was any medication given to or prescribed for the participant at this visit?.....  
0 = No  
1 = Yes → **LIST MEDICATIONS**  
\_\_\_\_\_  
\_\_\_\_\_

15. Final Cosmetic Result .....  
1= Regular  
2= Irregular  
3 =Scalloped (wavy)

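### Time to healing is a listed secondary outcome, but the required visits show only whether a man is healed at about day 28, and later follow-up of unhealed men is optional

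*Protocol*

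**What the plan says.** The Summary's list of secondary outcomes includes "time to healing; direct costs; post-operative pain; patient satisfaction; cosmetic result". It gives no definition or unit for the healing outcome. The same Summary says the study will show that the method is "safer for both surgeons and patients, heals sooner, has excellent cosmetic results".

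The scheduled visits are "7 days and 28 days", followed by "Optional 42 day follow-up if not completely healed by 4 weeks". The visit table in the Unicirc post-operative instructions lists the last visit as "6 weeks (optional", and the later follow-up form also labels it optional. The eligibility interview asks for "Willing to participate in 2 follow-up visits", and the flowsheet for potential participants has men agree to the 7-day and 4-week visits only.

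The Wound Healing section of the 4-week/optional 6-week form asks "Has the wound completely healed (no wound, completely epithelialized", answered yes or no. The form also records the post-operative day. It does not ask when healing occurred. The day-7 form and the unscheduled visit form, as shown, have no such item.

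**The concern.** A time to an event needs either the date of the event or looks close enough together to bracket it. Here the first look at healing is at about four weeks, and the only planned later one is optional and meant for men still unhealed.

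Two things are at stake. First, if most wounds in both arms close before day 28, the arms could differ by a week and look almost the same in the data. The claim of faster healing would then be untested rather than supported or refuted. Second, whether day-42 data are missing depends on the outcome, because only slow healers are offered that visit. If healing differs by arm, so may the missing data.

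**Working it through.** **What each man contributes.** The protocol states no figure for healing, so there is none to reproduce. From the forms:

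- Healed at the day-28 visit: healing time is at or before day 28, with no lower bound from a healing assessment.
- Not healed at day 28, attends day 42: healing time is between 28 and 42, or after 42.
- Not healed at day 28, skips day 42: healing time is known only to be after 28.

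That is at most three classes, and only the split at day 28 rests on a required visit. A median below 28 days cannot be estimated without a parametric assumption.

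**Men with no later healing status.** The arm sizes, 50 and 25, are from the Summary. The healing rates and the 50% skip rate are my assumptions. All men are taken to attend day 28.

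Men without later status = 0.5 × [50 × (1 − p_U) + 25 × (1 − p_C)], where p_U and p_C are the proportions healed at day 28 with Unicirc and open surgery.

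| Healed at day 28, Unicirc vs open | Unhealed men | Half skip day 42 | Share of 75 | By arm |
|---|---|---|---|---|
| 95% vs 90% | 2.5 + 2.5 = 5 | 2.5 | 3% | 1.25/50 = 2.5% vs 1.25/25 = 5% |
| 90% vs 70% | 5 + 7.5 = 12.5 | 6.25 | 8% | 2.5/50 = 5% vs 3.75/25 = 15% |
| 80% vs 50% | 10 + 12.5 = 22.5 | 11.25 | 15% | 5/50 = 10% vs 6.25/25 = 25% |

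**What a single look at day 28 gives up.** Assume lognormal healing times with a common log-SD s and medians m_U and m_C.

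- With exact times: power = Φ(|ln(m_U/m_C)| / (s√(1/50 + 1/25)) − 1.96).
- With day-28 status only: p = Φ(ln(28/m)/s) in each arm, then the exact power of a two-sided 5% Fisher test at 50 vs 25.

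For medians 18 vs 24 days and s = 0.3:

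- Exact times: 0.2877 / (0.3 × 0.2449) = 3.915; 3.915 − 1.96 = 1.955; power 0.975.
- Day-28 status: Φ(0.4418/0.3) = 0.93 vs Φ(0.1542/0.3) = 0.70; Fisher power 0.68.

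For medians 14 vs 21 days and s = 0.2, a one-week difference appears as about 100% vs 93% healed. Power is 0.29, against more than 0.99 with exact times.

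Five median pairs were tried (14/21, 18/21, 18/24, 21/28, 28/35) with s from 0.2 to 0.4. Exact-time power ran from 0.35 to above 0.99 and day-28 power from 0.16 to 0.98. The day-28 figure was lower in every scenario. Exact times are an upper bound that no clinic schedule reaches, so these gaps show the direction and the largest possible loss, not what a realistic schedule would recover.

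**The case against.** Several stronger readings are tempting, and the documents do not support them.

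- A reader might infer that healing time cannot be measured at all. That goes too far. The later form records the actual post-operative day next to healing status, which gives coarse interval-censored data. The form also allows for an unscheduled visit, so a status on another day could occasionally be captured. Such visits are unplanned, and the dedicated unscheduled form lacks the item, so this does not turn the data into a usable time to healing.
- A reader might infer that late attenders will be given falsely long healing times, since the day-7 form sets a 10-day maximum and the 4-week form sets no window. That bias arises only if visit day is used as healing day. The protocol does not say so, and the derivation may be in an analysis plan that is not shown.
- A reader might fault the day-7 form for having no healing item. The Unicirc instructions leave the tape on for 7 to 10 days, so the wound may still be covered at that visit. Leaving the item off is defensible.
- A reader might take 15% as the expected loss. It comes from the least favourable of three assumed scenarios.

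It can also be said that the analysis plan may settle all this. It can settle how to analyse the data. It cannot recover healing status that the schedule and forms do not collect. Finally, this is one of six secondary outcomes, which limits its weight.

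**Conclusion.** The point holds in this form: the protocol names a time-to-healing outcome and expects faster healing, while its required visits deliver only healed or not healed at about day 28. Differences before day 28 are largely invisible, and follow-up after day 28 is optional for exactly the men whose healing time is still open.

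The share of men with no later healing status is about 3% to 15% across the assumed scenarios. It is larger in the open-surgery arm in each of them because that arm was assumed to heal more slowly. These figures rest on assumed healing rates and an assumed 50% skip rate; the documents give neither. The facts about the visits and forms do not depend on them. The change should be made, but the primary outcome, intraoperative time, is unaffected.

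**What to change.** 1. Redefine the secondary outcome as complete healing at day 28 (yes/no), reported as a risk difference with 95% CI, and state a window for the day-28 visit.
2. Make the day-42 healing assessment expected rather than optional for men not healed at day 28. Include it in the visits men agree to at the eligibility interview and on the flowsheet, and align the post-operative instructions.
3. Limit any conclusion about faster healing to the proportions healed at day 28 and day 42.
4. If a time-to-event result is kept, analyse it as interval-censored using the recorded post-operative day.

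I would not add a complete-healing item at day 7. With tape possibly still in place in the Unicirc arm, ascertainment could differ by arm.

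The cost is protocol and form wording, a day-42 assessment for the men not healed (already planned as optional), and a more modest outcome label. The redefined outcome also has limited power at 50 vs 25. Exact two-sided 5% Fisher power is 0.69 for an assumed 80% vs 50% healed and 0.51 for 90% vs 70%, so the interval should carry the interpretation rather than a significance test.

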**WOUND HEALING**

**4. Did the participant have any difficulty keeping the wound clean and dry?** ..... |\_|\_|

0 = No  
1 = Yes

**5a. If YES, describe:** \_\_\_\_\_  
 \_\_\_\_\_

**5. Is there wound disruption or dehiscence?**..... |\_|\_|

0 = None    1 = < 2cm  
2 = More than 2 cm

**6. Is there any swelling?**..... |\_|\_|

0 = None    2 = Moderate  
1 = Mild    3 = Severe (if severe, report as Adverse Event)

**For Questions 7-11, if response is "moderate" or "severe," complete AE form and take a picture with participant's permission.**

**7. Is there any evidence of infection?**..... |\_|\_|

0 = None    2 = Moderate  
1 = Mild    3 = Severe

**8. Is there any bleeding?**..... |\_|\_|

0 = None    2 = Moderate  
1 = Mild    3 = Severe

**9. Is there a hematoma?**..... |\_|\_|

0 = None    2 = Moderate  
1 = Mild    3 = Severe

**10. Does the participant report difficulty or pain with urination?** ..... |\_|\_|

0 = None    2 = Moderate  
1 = Mild    3 = Severe

**11. Are there any other complications?**..... |\_|\_|

0 = None    2 = Moderate  
1 = Mild    3 = Severe

**13a. If response is 1, 2, or 3, describe complication:** \_\_\_\_\_  
 \_\_\_\_\_

**12. Was any medication given to or prescribed for the participant at this visit?**.....|\_|\_|

0 = No  
1 = Yes → **LIST MEDICATIONS**  
 \_\_\_\_\_  
 \_\_\_\_\_

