**17. What did you like about the circumcision?**

**18. What did you NOT like about the circumcision or what improvements would you suggest?**

**19. If the participant is either (1) newly identified as being completely healed at this visit, or (2) has an adverse event or is dissatisfied, does the participant permit us to take a picture of his penis?**.....|\_|

- 0 = No  
 1 = Yes (take a picture of penis)

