**1. Describe the Adverse Event:**

- List other:

- 9. Was additional suturing needed to treat this AE?**..... | \_\_\_\_\_  
 0 = No  
 1 = Yes  

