**9a. If YES, specify number stitches placed:**

- 14. Which supplies were used to treat this AE?**  
(Mark ☒ all that apply.)
- 17a.** Suture..... ☐
- 17b.** Bandages..... ☐
- 17c.** Catheter..... ☐
- 17d.** Drugs (List below)..... ☐
- 17e.** Drugs: \_\_\_\_\_ ☐
- 17f.** Other: \_\_\_\_\_ ☐

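### Post-operative pain is a declared secondary outcome, but the visible forms hold no pain rating and no count of analgesics taken

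*Protocol*

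**What the plan says.** The Protocol SUMMARY names intraoperative time as the primary outcome. The secondary list, after complications, reads "time to healing; direct costs; post-operative pain; patient satisfaction; cosmetic result". Pain appears by name only, without a scale, a time point or a source form.

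Follow-up is at 7 days and 28 days, with an optional visit at 42 days. The 7-day form allows up to day 10.

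Pain comes up in three other ways after surgery:

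- The 7-day, 4/6-week and Unscheduled Visit forms each ask "Does the participant report difficulty or pain with urination", graded 0 to 3. It is one of a run of complication items for which a moderate or severe answer triggers an adverse event form.
- The Post-Operative Instructions Unicirc tell the man "Take paracetamol, two tablets every 4-6 hours when needed for pain" and to make contact if pain increases. This is advice to the participant. No form asks how much he took.
- The acceptability questions at 4/6 weeks include the open item "What did you NOT like about the circumcision or what improvements would you suggest", where a man might mention pain unprompted.

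**The concern.** The protocol carries its own data collection forms, and those forms are where a named outcome becomes data. Operative time, complications, complete healing, cosmetic result and satisfaction each have an item. Post-operative pain does not.

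This differs from an outcome whose analysis is left to a later plan. If nobody asks a man to rate his pain, no analysis plan can supply the rating. Timing makes it worse: the first scheduled contact after the day of surgery is day 7, so pain in the first days is lost unless it is rated before discharge or asked by recall at day 7. A trial of a new technique against open surgery would then be unable to give a structured comparison on an outcome it listed.

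**Working it through.** No formula applies and the protocol gives no figure to reproduce. The check is a form-by-form reading of the Protocol for any item on wound pain, general pain or analgesic use after surgery.

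| Form | Visible numbering | Pain rating | Analgesics taken | Other mention of pain |
|---|---|---|---|---|
| Surgical Report Form, procedure page | not numbered | none | none | none; it holds anaesthetic use, blood loss, device size, time, notes and complications |
| Follow-up, 7 days | 1 to 12, no gap | none | none | "Does the participant report difficulty or pain with urination" (item 10) |
| Follow-up, 4 weeks and optional 6 weeks | item 4 not visible | none | none | same urination item (item 12) |
| Acceptability page, 4/6 weeks | 15 to 19 | none | none | open text only |
| Unscheduled Visit Form | 1 to 12, no gap | none | none | same urination item (item 10) |
| Adverse event form | jumps 1, 9, 14 | none visible | drugs used to treat the event only | none visible |

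**Can the urination item stand in for post-operative pain?** No. It combines difficulty with pain in one grade, concerns voiding and not the wound, and is built as a complication screen. At 4/6 weeks the healing question comes first, and a yes leads to "SKIP REST OF QUESTIONS", so healed men are not asked it at all.

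**Can the medication item stand in for analgesic use?** No. It appears on the 7-day, 4/6-week and Unscheduled Visit forms, but covers only what was given or prescribed at that visit. Tablets a man took at home under the instruction sheet are not counted.

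**Could the item sit in text that is not visible?** Some pages are absent from the available copy, including some near the Surgical Report Form, so a discharge rating cannot be ruled out with certainty. The 7-day and Unscheduled Visit forms have unbroken main numbering, so a lost item there is unlikely. The missing item 4 belongs to the 4/6-week visit, too late for early pain. The adverse event form is completed only when an event occurs, so it could not supply pain data for every man.

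**Count.** Planned men: 50 + 25 = 75. Structured post-operative pain items on the visible forms: 0. Men with a structured rating if the visible forms are followed: 0 of 75.

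**The case against.** The strongest reply is that absence is being argued from an incomplete copy, and that the forms leave room for pain to be written down. Each follow-up form has a graded item for any other complication with a description, there are comment fields, and there is the open acceptability question. This stands in part. It rules out saying that no information on pain could ever reach the database, or that the trial could report nothing on it. It does not supply a measure. Unprompted remarks are not asked of every man, have no common scale and cannot be compared fairly between arms.

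A reader might also infer three stronger things that the documents do not support.

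- *That direct costs are in the same position, recorded only through "Which supplies were used to treat this AE" and "Was additional suturing needed to treat this AE".* They are not. The Surgical Report Form records operating minutes, a first and any second surgeon, topical cream use, injected volumes and device size. Visit medication is listed whether or not there is an adverse event, and unscheduled visits have their own form. There is no routine consumables list, but unit prices can be applied later.
- *That the urination item will be reported as if it were post-operative pain.* Nothing in the Protocol says so.
- *That pain during the procedure should also be rated because the Unicirc arm uses topical anaesthetic.* The declared outcome is post-operative pain, and a score during surgery lies outside it.

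**Conclusion.** The point holds in this form: post-operative pain is a declared secondary outcome, and the visible forms contain no rating of it and no count of analgesics taken. Followed as written, they give a structured pain measure for no man in either arm, and an analysis plan cannot recover it afterwards.

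This rests on two assumptions: that the pages not available hold no pain item, and that no separate diary or questionnaire exists that the Protocol fails to mention. The unbroken numbering of the 7-day form supports the first for the visit that matters most, but cannot settle it for the day of surgery.

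The change should be made, but the point is not fatal. It concerns one secondary outcome and leaves the primary comparison of intraoperative time untouched.

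**What to change.** Add the following, with identical wording and timing in both arms:

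1. Surgical Report Form: one post-operative pain rating before discharge, for example 0-10, taken at a fixed interval after the procedure.
2. 7-day form: worst pain since surgery, current pain (same scale), and number of analgesic tablets taken since surgery.

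State the scale and these time points beside the outcome in the SUMMARY. If a pain item already exists on a page not seen here, cite it there instead. If the sponsor does not want to collect pain, remove post-operative pain from the secondary outcomes.

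The cost is four form items and about a minute per visit. Worst pain and tablet count at day 7 rest on recall over 7 to 10 days, and a discharge rating may partly reflect residual anaesthesia. Both limits should be acknowledged when the results are read. Sample size, visit schedule and primary analysis do not change.

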## **CIRCUMCISION RANDOMIZED CONTROLLED TRIAL**

Subject Number : \_\_\_\_\_

Date when entered study: \_\_\_\_\_

Date of Circumcision: \_\_\_\_\_

Date of follow-up done:

Date of next follow-up visit

1. \_\_\_\_\_

\_\_\_\_\_

2. \_\_\_\_\_

\_\_\_\_\_

3. \_\_\_\_\_

\_\_\_\_\_

4. \_\_\_\_\_

\_\_\_\_\_

|----------------|-------------------------------------------------------------------------------------------------------------|----------------------------------------------------------------------------------------------------------------------------------------------------------------------------------------------------------------------------------------------------------------------------------------------------------------------------------------------------------------------------------------------------------------------------------------------------------------------------------------------------------------------------------------------------------------------------------------------------------------------------------------------------------------------------------------------------------------------------------------------------------------------------------------------------------------------------------------------------------------------------------------------------------------------------------------------------------------------------------------------------------------------------------------------------------------------------------------------------------------------------------------------------------------------------------------------------------------------------------------------------|--------------|--|---|-------------|--|---|---|---|---|--|---|--|------------|--|--|--------------|--|--|-------------|--|--|--|--|--|
| Center: | Study Staff Name:

 | Date of Visit:

 	 	 / 	 	 	 / 	2	 	0	 	1	 	

Day	Month	Year	

 |              |  | / |             |  | / | 2 |   | 0 |  | 1 |  | Day |  |  | Month |  |  | Year |  |  |  |  |  |
|                |                                                                                                             | /                                                                                                                                                                                                                                                                                                                                                                                                                                                                                                                                                                                                                                                                                                                                                                                                                                                                                                                                                                                                                                                                                                                                                                                                                                                  |              |  | / | 2           |  | 0 |   | 1 |   |  |   |  |            |  |  |              |  |  |             |  |  |  |  |  |
